#### 3.3.7. Sample Size

For sample and power calculations, this study is powered on changes in total body fat assessed by DXA. We consider a type I error of 5% and a power of 80% (using the software GPower version 3.1.9.2) to detect an effect size of 0.58 for statistically significant differences in total body fat as reported elsewhere [78]. A total of 37 participants per group will be required. Considering a 20% drop out rate, as occurred in the selected study [78], we will enroll 94 participants (47 in each group).

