#### 3.3.6. Statistics

Statistical analysis will be performed using IBM SPSS statistics version 24.0 (IBM, Chicago, IL, USA). To test the normality of distribution of the variables, the Kolmogorov–Smirnov test will be performed. Descriptive statistics will be calculated (mean, standard deviation, and range). If normality is not achieved in some variables, non-parametric methods will be used. Repeated measures with Bonferroni corrections for adjusted comparisons will be used to determine any differences between conditions at the three moments and for changes between the intervention and control groups over time in primary and secondary outcomes. For exploring the association between changes in body composition and metabolic parameters, linear mixed regression models will be conducted. Statistical significance will be set at *p* < 0.05.

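### With the test and its tails unstated, 37 per group is close to the one-sided 5% answer; under a two-sided 5% two-sample t-test it gives about 69% power, not 80%

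*Protocol article*

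**What the plan says.** Section 3.3.7 (Sample Size) fixes the endpoint: "this study is powered on changes in total body fat assessed by DXA". It sets the error rates ("We consider a type I error of 5% and a power of 80" per cent), names the program ("using the software GPower version 3.1.9.2") and gives the target: "to detect an effect size of 0.58 for statistically significant differences in total body fat". The result is "A total of 37 participants per group will be required". A 20% drop-out allowance then brings enrolment to 47 per group, 94 in total.

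The section does not say which test was selected in the software, whether it was one- or two-sided, or whether a correlation between repeated measurements was assumed.

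Section 3.3.6 (Statistics) plans repeated-measures comparisons with Bonferroni correction, looking for a difference of any kind between conditions at the three assessments and between groups over time. "Statistical significance will be set at" p < 0.05. The term two-sided does not appear, and neither does any announcement of a one-sided test.

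**The concern.** A reader who enters the stated inputs into an ordinary two-sided two-sample calculation gets 47 or 48 per group, not 37. The same inputs in a one-sided calculation give 37 or 38. The sample size therefore appears to rest on a more lenient test than the non-directional one described one section earlier.

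What is at stake is the reading of a null result. If total body fat shows no significant difference, the trial will be read as having had a 20% chance of missing an effect of 0.58. Under a two-sided test on the planned evaluable number, that chance is about 31%. Type I error and the validity of the comparison are not affected.

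**Working it through.** **Inputs.** From Section 3.3.7: alpha 0.05, power 0.80, effect size 0.58, 37 per group, 20% drop-out, 47 per group enrolled. Equal allocation follows from 47 in each group. Two readings are mine: 0.58 is a standardised mean difference d for change, and the comparison is a two-sample test between groups.

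**1. Reproducing 37.** Normal approximation: n per group = 2(z_alpha + z_power)² / d².

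- One-sided 5%: 2(1.645 + 0.842)² / 0.58² = 36.8, rounded up to 37.
- Two-sided 5%: 2(1.960 + 0.842)² / 0.58² = 46.7, rounded up to 47.

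**2. The same with the noncentral t.** Degrees of freedom are 2n − 2 and the noncentrality is d√(n/2). For n = 37 the noncentrality is 0.58 × √18.5 = 2.495, on 72 degrees of freedom.

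| Test at 5%, d = 0.58 | n per group | Power |
|---|---|---|
| One-sided | 37 | 79.6% |
| One-sided | 38 | 80.5% |
| Two-sided | 37 | 69.2% |
| Two-sided | 47 | 79.5% |
| Two-sided | 48 | 80.3% |

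The exact one-sided requirement is 38 and the exact two-sided requirement is 48. Power of 69.2% means a type II error of 30.8%.

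**3. Could rounding of the effect size explain it?** At the top of the range that rounds to 0.58 (just under 0.585), two-sided power with 37 per group is still only 69.9%. One-sided, 37 is enough once d is about 0.584. Rounding can therefore close the one-sided gap of one participant per group, but not the two-sided gap of eleven (48 − 37).

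**4. Effect detectable with 37 per group.** Solving the two-sided noncentral t for 80% power gives d = 0.66.

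**5. Drop-out step.** 37 / 0.8 = 46.25, rounded up to 47 per group and 94 in total. This step is correct. In the other direction, 47 × 0.8 = 37.6, so about 37 evaluable per group is what the plan itself expects.

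**6. What 80% would take, two-sided.** 48 / 0.8 = 60 enrolled per group, 120 in total.

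**The case against.** The strongest objection is that the origin of 37 is not established. The section is silent on the test, and two-sidedness is inferred from the non-directional wording of Section 3.3.6. The one-sided explanation is also not exact: the noncentral t gives 38 at d = 0.58, so 37 needs either the normal formula or an unrounded effect of about 0.584.

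There is, moreover, a two-sided route to 37 within the family of methods that Section 3.3.6 names. A repeated-measures between-group F test with f = 0.58 / 2 = 0.29 needs 37 per group if the correlation between measurements is about 0.52 to 0.54 (two measurements) or about 0.64 (three). Similarly, a baseline-adjusted analysis of covariance would reach 80% with 37 per group if the baseline correlation were about 0.48 and 0.58 were an unadjusted effect.

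Part of this stands. A reader might infer that the authors ran a one-sided test; the article does not show that, and 37 does not arise only that way. But neither alternative rescues the stated power. No correlation is given. The between-group repeated-measures test compares means averaged over visits, whereas the trial is powered on change. No analysis adjusted for baseline fat is described: the adjusted comparisons in Section 3.3.6 are the Bonferroni ones, and the Discussion promises control for age, years since retirement and sex. For the same reason one cannot say that baseline adjustment will recover part of the lost power.

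A stronger reading in the other direction is that the Bonferroni correction pushes power lower still. Dividing alpha by three would give about 52% at 37 per group, but the article states no divisor and does not say that the main between-group test is corrected this way. That figure is an assumption and forms no part of this point.

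**Conclusion.** The 80% power claimed in Section 3.3.7 is not supported by the inputs given beside it when the comparison is non-directional, as Section 3.3.6 describes. Under a two-sided 5% two-sample t-test with d = 0.58, power at the planned 37 evaluable per group is about 69%, a shortfall of roughly 11 percentage points. Only full retention brings it close to target, at 79.5%, so the allowance for drop-out is in effect used up.

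The conditional arithmetic is firm. It rests on three assumptions: 0.58 is Cohen's d for change, the groups are compared without covariate adjustment, and the test is two-sided. The explanation that 37 came from a one-sided calculation is the closest simple match, but it remains an inference.

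**What to change.** In Section 3.3.7, name the test, state the two-sided 5% level, and give any correlation that was assumed. If no undisclosed assumption accounts for 37, restate the result along these lines:

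> For a two-sided 5% two-sample t-test, 37 evaluable participants per group (94 enrolled, 20% drop-out) give about 69% power for d = 0.58 and 80% power for d = 0.66.

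Keep enrolment at 94. Do not resolve the mismatch by declaring the test one-sided at 5% afterwards: that is equivalent to a two-sided 10% level and would conflict with Section 3.3.6. The restatement should not claim a gain from baseline adjustment unless such an analysis is specified.

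The cost is a sentence or two of wording and a less favourable power figure. No participants or procedures are added. Restoring 80% for d = 0.58 would instead need 120 enrolled, 26 more than planned; the correction does not require this.

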## 4. Discussions

This paper describes the protocol of the Champ4life project, a study that aims to develop an effective lifestyle intervention for former athletes with overweight and obesity.

The ending of a sports career is inevitable, and athletes are often faced with challenges to adapt to their new lifestyle. It is expected that when an athlete reduces his/her PAEE, an equivalent reduction in his/her EI occurs. However, the current literature shows that a sedentary routine does not induce a compensatory reduction in E, showing that former athletes will likely feel challenged in the adaptation to their new reality as regards to their PA and food choices routines. The effect of a lifestyle intervention on former athletes that have become inactive and gained excessive weight is still understudied.

This will be the first randomized clinical trial spanning a one-year intervention period aimed at understanding the effects of a lifestyle intervention on multiple health outcomes in former athletes. By empowering participants with key knowledge, forming the basis for informed decisions, and most of all, with a set of central self-regulatory skills (self-monitoring, action planning, and goal setting), it is expected that there will be an effective promotion of sustained improvements in body composition (especially by reducing total and abdominal FM), metabolic markers, health-related quality of life [79], and physical function [80].

According to the Endocrine Society, only a low percentage of people who lose weight (<20%) are able to maintain it [81], despite the effectiveness of common strategies in the short-term. In fact, the first year after the weight loss is the most challenging, with one-third of the lost weight tending to be regained over that year [82].

Two years after weight loss, 40% of the people who achieved a modest weight loss (at least 5% of initial weight), regained at least half of their lost weight during the maintenance period [81]. The current program is based on SDT, which has been previously proven effective in the promotion of long term behavioral changes and weight-loss [30,32,83]. This program will focus on the promotion of participant’s autonomous motivation towards their weight management process and on the provision of useful knowledge and tools to help them sustain their healthy behaviors. Therefore, successful maintenance of the positive lifestyle changes and lost weight is expected.

In addition, prior research has shown an increase in upper and lower body strength after diet and exercise programs [84]. Other studies have shown that after lifestyle interventions, an increase of cardiorespiratory fitness occurs [84,85,86]. Therefore, it is expected that after the Champ4life intervention, participants reveal an increase in physical fitness, leading to higher muscle quality, better cardiorespiratory fitness, and lower mortality [86].

We also expect to understand the metabolic and behavioral compensations that may occur during weight loss and maintenance. We aim to find any compensations which lead to the retake of initial weight, like changes in energy intake and expenditure [20], spontaneous PA [21], and adaptive thermogenesis [22]. The current literature shows that when we increase EE (by increasing PA), we may compensate by increasing sedentary behavior, decreasing lifestyle PA and/or increasing energy consumption during the rest of the day [87]. The mechanisms underlying adaptive thermogenesis (i.e, mainly the decrease in REE and PAEE), beyond what can be predicted from the changes in FM and FFM in response to a restricted EI [19], are unclear when modest weight loss is expected. The mechanisms underlying the interplay between PA and alterations in eating behaviors and dietary intake (in terms of quantity and quality) also require further exploration, in order to improve interventions’ efficacy.

A significant strength of the Champ4life program will be the SDT-based intervention, providing tools for the adoption and sustainability of healthy behaviors through the development of autonomous motivation and self-regulatory skills [30,32,83]. Some limitations are anticipated in this study and should be addressed, in particular the effect of confounding variables such as the large age range (18–65 years) of participants eligible to be included, retirement years, and an unbalanced gender representation, provided there are more male former athletes than females.

To address these issues, the analysis will be controlled for the potential effects of these confounders. In addition, the prevalence of eating disorders is higher among athletes, especially in those engaged in weight-sensitive sports [88,89], and this may also be the case with former athletes; still, this aspect might not be appropriately captured by initial screening procedures (relying on yes/no answers) and thus will constitute a limitation of the present study.

We are also expecting to find barriers in the recruitment process due to the inclusion criteria. Despite the adherence promotion efforts, we may have some difficulties in retaining the participants throughout the study, due to its duration (~1 year), in particular those randomized to the control group. To minimize this risk, the control group is, in fact, a waiting list comparison group that is offered the program after the 12-month follow-up.

In conclusion, we anticipate that Champ4Life will be a novel and unique approach to improve athletes’ healthy lifestyle in post-career life. This project will provide evidence on the effectiveness of the Champ4Life program delivered to former athletes and will offer insight on the impact of changing PA, sedentary behavior, and diet on body composition and secondary outcomes, such as EB regulation and overall health-related markers. The findings from this project will enable evidence-based decisions for the implementation of lifestyle interventions for post-career transition.

## Figures and Tables

**Figure 1 nutrients-12-00286-f001:**
[figure not shown]
Schematic description of the study phases.

**Table 1 nutrients-12-00286-t001:** Schematic description of all measurements.

	M_1_			M_2_		M_3_		
Schedule	Visits 1 and 2 *		Visit 3	Visit 1		Visit 1		Visit 2
08:00–08:45	REE and Blood pressure	Fasted stage	Strength tests	REE and Blood pressure	Fasted stage	REE and Blood pressure	Fasted stage	Strength tests
08:45–09:00	Blood samples		Questionnaires (IES-2; REBS; BREQ-3; SF-36)	Blood samples		Blood samples		Questionnaires (IES-2; REBS; BREQ-3; SF-36)
09:00–09:20	DXA			DXA		DXA		
09:20–09:40	Bioimpedance		Cardiorespiratory fitness test	Bioimpedance		Bioimpedance		Cardiorespiratory fitness test
09:40–10:10	Anthropometry			Anthropometry		Anthropometry		
10:10–10:30	LFPQ			LFPQ		LFPQ		
10:30–10:45	BREAK			BREAK		BREAK		
10:45–11:00	Delivery of the motion sensors and food diaries with face-to-face instructions.			Delivery of the motion sensors and food diaries with face-to-face instructions.		Delivery of the motion sensors and food diaries with face-to-face instructions.		
11:00–11:45				Questionnaires (IES-2; REBS; BREQ-3; SF-36)				

Legend: Baseline (M1), Moment 2 (M2), and Moment 3 (M3); E_1_—first evaluation; E_2_—second evaluation; E_3_—third evaluation; REE—resting energy expenditure; DXA—dual-energy X-ray absorptiometry; IES-2—Intuitive Eating Scale—2; REBS—Regulation of Eating Behavior Scale; BREQ-3—Behavioral Regulation in Exercise Questionnaire—3; SF-36—Short-Form Health Survey; LFPQ—Leeds Food Preference Questionnaire. * At baseline (M1) the first visit starts with the delivering of the accelerometer, given that the physical activity level of the participants is required for assessing eligibility.

**Table 2 nutrients-12-00286-t002:** Eligibility criteria.

**Inclusion Criteria**
Former high-level athlete; Aged 18–65 years (male or female); Inactive (<20 min/day of vigorous physical activity intensity for at least 3 days per week or <30 min/day of moderate intensity physical activity for at least 5 days per week [39]); With overweight/obesity (BMI ≥25 kg/m^2^); Available to participate in the educational sessions at FMH-UL; Ready to modify their diet in order to lose body weight.

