## Abstract

Preventive and educational programs directed to former elite athletes in the areas of healthy living are required. This is particularly relevant as obesity and health-related problems are observed in retired athletes, especially in those whose current levels of physical activity are below the recommendations. During their sports career, elite athletes are supported by a multidisciplinary team; upon retirement, no support is provided for the transition to a different lifestyle. So far, no program has been implemented to promote sustained healthy lifestyle behaviors in the post-career transition and evidence is lacking for such an intervention. Firstly, we aim to determine if Champ4life, a 1-year lifestyle intervention targeting inactive former athletes with overweight and obesity, is effective for reducing total and abdominal fat. Secondly, our purpose is to assess the effectiveness of the intervention on the levels of physical activity and sedentary behavior, resting energy expenditure, cardio-metabolic markers, physical fitness, energy balance components, eating self-regulation markers, and quality of life over 12 months. Champ4life is an evidence- and theory-based program using a randomized control trial design (intervention vs. control group) that will be conducted on 94 inactive former elite athletes with overweight and obesity. The first four months of the Champ4Life program include a nutritional appointment and 12 weekly, 90-min sessions. Classroom sessions seek to provide participants with key information and a toolbox of behavior change techniques to initiate and sustain long-term lifestyle changes. Participants will undergo baseline, 4-month, and 12-month measurements of body composition (primary outcomes), resting energy expenditure, physical fitness, metabolic markers, energy balance related-markers, and quality of life (secondary outcome). This trial will provide evidence on the effectiveness of the Champ4life program, a pioneer lifestyle intervention for retired athletes, offering tools for sustained changes in physical activity, sedentary behavior and diet, aiming to improve body composition and overall health-related markers.

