### 2.2. Sample Recruitment and Selection

A total of 94 healthy participants of both genders will be selected. The Portuguese Olympic Committee, the Union of Professional Soccer Players, and several national sports federations (Portuguese Judo Federation, Portuguese Swimming Federation, Portuguese Football Federation, and Portuguese Wrestling Federation) are partners of this project, and will able to recruiting former top-level athletes through direct mail, databases, and referral sources provided by these institutions. Media advertising is also planned. Brochures and posters summarizing the goals of the study, procedures, and measures to ensure participant safety will be created. Following an initial web and/or telephone screen to determine the eligibility of potential participants, an orientation session will be scheduled to offer detailed information about the study will be provided, including the number and type of assessments, the length and nature of the exercise training and the time commitment required to complete the study. The eligibility criteria are described in Table 2. A “yes” or “no” question was used to evaluate if participants did not report any exclusion criteria.

Next, potential participants will undergo run-in visits meant to reduce attrition by allowing them to determine if they will be able to schedule the study into their weekly routine. All run-in sessions must be completed within a 1-week period to satisfy the eligibility criteria. During the screening, staff members will verify that eligible participants are not currently meeting public health PA guidelines and obtain their informed consent to participate in the study.

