### 2.3. Screening Process

The purpose of the staged screening process is to (1) verify eligibility; (2) obtain the participant’s informed consent; (3) complete baseline measurements; and (4) perform randomization.

The study will include several screening steps before randomization:A preliminary screen will be completed to determine eligibility either by phone or at the FMH-UL in separate visits to eliminate a substantial proportion of ineligible volunteers;Debriefing session for potential participants will be provided at FMH-UL with information about the study, including clarification of possible questions;Visit 1, taking place at FMH-UL, will consist of a physician appointment and a first informed consent form required for laboratory visit 1. It should be completed within 1 week after the debriefing session;Laboratory visit 1 will be required for participants to use accelerometers for PA assessment, individual calibration of motion sensors, and to fill dietary records (1 week). Successful completion will be required for eligibility. A second informed consent will be obtained for visits 2 and 3, which must be completed within 1 week;Laboratory visits 2 and 3 will include body composition, resting energy expenditure, physical fitness measurements, blood sample collection, eating-related measurements, and the completion of an exercise motivation questionnaire and a quality of life questionnaire. At the end, a third informed consent will be obtained to allow program enrollment.

Flexibility and alternative approaches in scheduling these steps are expected due to varying local circumstances, but all screening procedures will take place before randomization to guarantee each participant’s eligibility. Additional screening visits may be required due to time constraint issues.

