### 3.2. Free-Living Physical Activity and Energy Expenditure

#### 3.2.1. Accelerometry

All participants will be asked to wear an accelerometer ActiGraph GT3X+ (ActiGraph, Pensacola, FL) to assess the amount of activity expressed as minutes per day spent in different intensities. The accelerometer will be placed on the right hip, near the iliac crest, during waking-hours, and requested to be removed only during water-based activities such as showering and swimming [53]. The device activation, download, and processing will be performed using the software Actilife (v.6.9.1). The cutoff values used to define the intensity of PA and therefore to quantify the mean time in each intensity (sedentary, light, moderate, or vigorous) will be as follows: sedentary: <100 counts·min^−1^; light: 100–2019 counts·min^−1^; moderate: 2020–5998 counts·min^−1^ (corresponding to 3–5.9 METs); vigorous: ≥5999 counts·min^−1^ (corresponding to ≥6 METs) [54]. Participants will be included if they had a total of at least three valid days of accelerometer data. A valid-day will be defined as having 600 or more minutes (≥10 h) of monitor wearing, corresponding to the minimum daily use of the accelerometer [55]. Apart from accelerometer non-wearing-time (i.e., when it is removed for sleeping or water activities), periods of at least 60 consecutive minutes of zero activity intensity counts will also be considered as non-wearing-time [56]. An Actigraph break will be considered as any bout of time in which the accelerometer count rises up to or above 100 counts·min^−1^ and which stays within the light-intensity physical activity (LIPA) range (<2020 counts·min^−1^). There are no cutoffs for the sedentary-time using the three-axial information from this new generation Actigraph GT3X+ accelerometer; therefore, we will use the previous cutoffs, which utilize the vertical-axis information only.

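### Table 2's definition of inactive is met by failing either one of two activity thresholds, which contradicts the screening rule that participants must not be meeting activity guidelines

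*Protocol article*

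**What the plan says.** The trial is to be "conducted on 94 inactive former elite athletes with overweight and obesity", and the primary aim in the Introduction is framed for the same inactive population.

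Two places say who counts as inactive:

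- **Table 2, inclusion criteria:** "Inactive (<20 min/day of vigorous physical activity intensity for at least 3 days per week or <30 min/day of moderate intensity physical activity", with the moderate limb reading in full "<30 min/day of moderate intensity physical activity for at least 5 days per week".
- **Section 2.2, Sample Recruitment and Selection:** during screening, "staff members will verify that eligible participants are not currently meeting public health PA guidelines".

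Activity for this purpose is measured by accelerometer. The Table 1 footnote says that the device is handed out first at baseline, "given that the physical activity level of the participants is required for assessing eligibility". Section 2.3 provides for one week of accelerometer wear and dietary records and adds "Successful completion will be required for eligibility". Table 2 also excludes candidates who do not complete the dietary and activity run-in. In the measurement chapter, section 3.2.1 says "Participants will be included if they had a total of at least three valid days of accelerometer data", and "A valid-day will be defined as having 600 or more minutes (≥10 h) of monitor wearing".

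**The concern.** Table 2 pairs a vigorous threshold with a moderate threshold, which looks like a guideline that can be met by either route. A person fails such a guideline only by failing both routes. Table 2 asks for failure of one.

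Two screeners could then decide differently about the same person, one by applying Table 2 and the other by applying section 2.2. Inactivity defines the population in the abstract and in the primary aim. If the rule is ambiguous, a later reader cannot tell to whom the result applies. Randomisation is not affected, so this is a matter of which population is studied and not of bias between the groups.

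**Working it through.** The plan gives no figure of its own on this point, so the check is one of logic, made concrete by listing cases.

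**Inputs.** Vigorous threshold: 20 min/day, 3 days/week. Moderate threshold: 30 min/day, 5 days/week (both Table 2). Screening rule: eligible people are not meeting guidelines (section 2.2). Moderate and vigorous are separate count bands, 2020–5998 and 5999 or more counts/min (section 3.2.1).

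**Assumption.** The guideline is met by either route. Let v be the number of days with at least 20 min vigorous and m the number with at least 30 min moderate, each from 0 to 7. The guideline is met if v ≥ 3 or m ≥ 5.

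**Step 1, logic.** Not (A or B) equals (not A) and (not B). Table 2 prints (not A) or (not B). The less-than sign appears in both limbs, so the sentence cannot be read as one negation covering both.

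**Step 2, one candidate.** Take 60 min/day in the moderate band on 7 days and no vigorous minutes: v = 0, m = 7. The vigorous limb of Table 2 is satisfied, so this person is inactive. Since m ≥ 5, the guideline is met and section 2.2 rejects the same person.

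**Step 3, all patterns.** There are 8 × 8 = 64 pairs (v, m).

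- Not meeting the guideline: v ≤ 2 and m ≤ 4, so 3 × 5 = 15. Meeting it: 64 − 15 = 49.
- Table 2 with the day counts read as intended (v ≤ 2 or m ≤ 4): only v ≥ 3 together with m ≥ 5 is shut out, 5 × 3 = 15. So 49 qualify, and 49 − 15 = 34 of these meet the guideline.
- Table 2 with the day counts read word for word: fewer than 20 min on at least 3 days means 7 − v ≥ 3, so v ≤ 4. Fewer than 30 min on at least 5 days means 7 − m ≥ 5, so m ≤ 2. With *or*, only v ≥ 5 together with m ≥ 3 is shut out, 3 × 5 = 15. Again 49 qualify and 34 meet the guideline.

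**Step 4, is changing the conjunction enough?** The word-for-word day counts joined by *and* (v ≤ 4 and m ≤ 2) admit 5 × 3 = 15 patterns, but not the right 15. They admit 2 × 3 = 6 that meet the guideline (v = 3 or 4, m = 0 to 2) and shut out 3 × 2 = 6 that do not (v = 0 to 2, m = 3 or 4). Someone vigorously active on 4 days, for instance, still has 3 days below 20 minutes.

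**Step 5, the reworded criterion.** Failing both routes (v ≤ 2 and m ≤ 4) admits exactly the 15 non-meeting patterns and none of the 49 others. This agrees with section 2.2.

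**Step 6, valid days.** With 3 or 4 valid days, the number of active days that can be seen is at most 3 or 4. A count of 5 moderate days could then not be observed. This matters only if the minimum in section 3.2.1 is also applied at screening.

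**The case against.** The strongest reply is that section 2.2 is a second check. If staff apply it as well as Table 2, the daily moderate exerciser is turned away. The intent is also plain, so the *or* could be read as loose wording. This stands in part. A reader might infer from Table 2 that guideline-meeting people will be enrolled, but the documents do not support that. They show only that the two statements disagree. Plain intent does not repair a criterion that is printed in full and says something else.

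The guideline cited in Table 2 is not reproduced, so its either/or form is inferred from the paired thresholds. That is a fair caveat and is carried into the conclusion.

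A reader might also infer that three valid days are enough to establish eligibility. The three-day rule sits in the measurement chapter, among the processing rules for activity data. The screening text asks for a completed one-week run-in and does not say that three days count as completion. The inference is therefore not established.

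Finally, a reader might infer a diluted effect on fat mass. Nothing in the documents allows this to be sized. All participants have a BMI of at least 25 and must be ready to change their diet, and the programme includes a dietary reduction. The documents do not show that someone who meets one activity threshold would lose less fat.

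**Conclusion.** The point holds as a contradiction between two eligibility statements. As worded, Table 2 accepts anyone who falls short on one of two thresholds, while section 2.2 requires that the guideline not be met at all. Under the either/or assumption, 34 of the 49 weekly patterns that Table 2 admits meet the guideline. The count is the same whether the day counts are read as intended or word for word. It describes the reach of the wording; it does not estimate the share of candidates affected, for which the documents give no basis.

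The day counts are a second fault in the same sentence, so a change of conjunction alone would leave errors in both directions. The valid-day question is secondary and conditional on the three-day minimum being used at screening.

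**What to change.** Reconcile Table 2 with section 2.2 by rewording the inclusion criterion with its own thresholds: *meets neither at least 20 min/day of vigorous activity on at least 3 days per week nor at least 30 min/day of moderate activity on at least 5 days per week*. Use the same sentence on the screening form.

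Also make clear that the three-valid-day minimum in section 3.2.1 applies to outcome data and is not relied on for eligibility, which rests on the completed one-week run-in.

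The cost is one amended line and one clarifying sentence. A few candidates who would pass the present Table 2 become ineligible; where section 2.2 is already applied, nobody is lost.
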